#### Healthcare providers

The Assessment Chronic Illness Care (ACIC) questionnaire, which is a tool to measure the level of care integration according to healthcare providers [38], was sent to primary care providers at baseline and is evaluated at 12 months. Furthermore, we use a self-designed questionnaire at 12 months (“Satisfaction, involvement and implementation of the IDM program”) for the primary care team, to measure the level of involvement and implementation of the practice teams with the RECODE intervention at 12 months. This questionnaire comprises questions on the number and type of healthcare providers which were involved in the program, the types of team meetings and local appointments, and the usage of tailored benchmark reports. Furthermore, we requested the number of patients involved in the intervention, and the numbers of components implemented in daily practice. Overall, the healthcare providers are asked to rate the intervention on a 5-point scale, and we ask for details on possible bottlenecks and problems regarding implementation.

#### Current level of care of the practices at baseline

The current level of COPD care was assessed at baseline in all general practices to be able to report any difference in quality of care at 12-months follow-up. Therefore, from the EMRs we extracted the following performance indicators: registration of smoking status and stop-smoking advice, registration of body mass index, assessment of spirometry and inhalation technique in the last year, the number of patients with monitored functioning by means of the CCQ, MRC, or the number of patients with controlled physical activity in the last year.

### Sample size calculation

The primary outcome is the difference in change in the CCQ score between baseline and 12 months between both groups. We used methods for standard sample size estimates for trials that randomised at the level of the individual [39] adjusting for clustering by inflating sample size estimates by the design effect given by 1 + (n-1)ρ, where n is the average cluster size, and ρ is the estimated intraclass correlation coefficient (ICC) [40]. Sample size estimates are based on the mean difference in CCQ between intervention and control group. Using the minimal clinically important mean difference for the CCQ [29], and the upper value of 0.05 from a range of ICC values identified in studies involving the older person in primary care [41], power calculations indicate that 40 clusters of practices with an average of 27 participants per cluster are required. To allow for subgroup analysis in MRC scores 1–2 versus 3–5, in total 1080 participants are need to be randomized to achieve a power of at least 80% with alpha levels of 0.05, including a participant loss to follow-up of 10% or a loss of 4 clusters at 12 months.

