**Methods/design:**

RECODE is a cluster randomized trial with two years of follow-up, during which 40 clusters of primary care teams (including 1086 COPD patients) are randomized to IDM or usual care. The intervention started with a 2-day multidisciplinary course in which healthcare providers are trained as a team in essential components of effective COPD IDM in primary care. During the course, the team redesigns the care process and defines responsibilities of different caregivers. They are trained in how to use feedback on process and outcome data to guide implement guideline-driven integrated healthcare. Practice-tailored feedback reports are provided at baseline, and at 6 and 12 months. The team learns the details of an ICT program that supports recording of process and outcome measures. Afterwards, the team designs a time-contingent individual practice plan, agreeing on steps to be taken in order to integrate a COPD IDM program into daily practice. After 6 and 12 months, there is a refresher course for all teams simultaneously to enable them to learn from each other’s experience. Health status of patients at 12 months is the primary outcome, measured by the Clinical COPD Questionnaire (CCQ). Secondary outcomes include effects on quality of care, disease-specific and generic health-related quality of life, COPD exacerbations, dyspnea, costs of healthcare utilization, and productivity loss.

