### Primary outcome

The primary outcome measure in this study is health status as measured by the Clinical COPD Questionnaire (CCQ) at 12 months. This questionnaire is a disease-specific, 10-item questionnaire that calculates an overall score and three domain scores: symptoms, functional state and emotional state. Patients are required to respond to each item on a 7-point scale with 0 representing the best possible score and 6 representing the worst possible score. This instrument is proven to be sensitive and valid, and easy to administer in primary care. The minimal clinical important difference (MCID) is −0.4 points [29,30].

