### Informed consent

Informed consent was provided by the GPs and the patients. The informed consent was acquired before the course took place and the practices started with their intervention.

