### Non-participation analysis

As we invited all eligible participants for this trial with an invitation letter with an attached CCQ questionnaire, we were able to determine any differences between participants of the trial and COPD patients eligible but declining randomization, in order to assess external validity (Table 5). Of all eligible patients who were invited to participate, 1549 questionnaires had analyzable data. We received a higher response rate (961 vs. 588) of returned CCQ questionnaires in the group of patients willing to participate in the trial, compared to patients eligible but declining randomization. There was no difference in age between both groups. Significantly more men (54.7%) are participating in the RECODE trial compared to the proportion of men in patients who declined participation (46.9%). Furthermore, participants in the trial reported significantly more symptoms and disabilities on their functional and mental state, which was reflected in a mean total CCQ score of 1.8 (1.1), compared to 1.5 (1.1) in non-participants.

**Table 5 T5:** Characteristics and comparison of participants and non-participants of the RECODE trial

	**Participant (n = 961)***	**Non-participant (n = 588)**	**p-value**
**Age, years (SD)**	68.7 (11.0)	67.8 (11.5)	0.162
**Males,%**	54.7	46.9	0.003

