### Baseline characteristics COPD patients

Table 6 presents the baseline demographic and clinical characteristics of the included COPD population. Enrolled subjects were mainly elderly (ex) smokers, and had moderate COPD which is reflected by a mean post-bronchodilator FEV1 of 68% predicted. We included COPD patients with substantial co-morbidities: 36.8% had a diagnosis of hypertension, 16.1% suffered from major cardiovascular disease, 14.7% had diabetes and 9.9% had a combined diagnosis of depression. Mean SGRQ total score was 35.6 (20.5) and mean CCQ total score was 1.5 (0.97). The proportion of patients with dyspnea on moderate exertion or worse (MRC score >2) comprised one third of the study population.

**Table 6 T6:** Baseline demographic and clinical characteristics of the patients with COPD included in the RECODE study

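### The primary outcome is given both as 12-month CCQ and as change in CCQ; one baseline-adjusted estimate would remove the conflict and gain precision at no cost

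*Protocol article*

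**What the plan says.** In the Protocol article, the Primary outcome section states: "The primary outcome measure in this study is health status as measured by the Clinical COPD Questionnaire (CCQ) at 12 months". The Abstract agrees: "Health status of patients at 12 months is the primary outcome, measured by the Clinical COPD Questionnaire (CCQ"). The Sample size calculation section gives a different definition: "The primary outcome is the difference in change in the CCQ score between baseline and 12 months between both groups". Two sentences later it adds "Sample size estimates are based on the mean difference in CCQ between intervention and control group", without saying whether that mean is of the 12-month score or of the change.

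The Secondary outcomes section lists CCQ again, at time points that include 12 months, under changes in health-related quality of life. Read literally, the 12-month change in CCQ is secondary there and primary in the sample size section.

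The section on analysis of effectiveness commits to intention to treat and to a multi-level model that respects clustering. It names no response variable and no covariates, and it neither states nor excludes adjustment for baseline CCQ. Table 2 schedules CCQ at baseline and at 12 months.

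**The concern.** A primary outcome should lead to one number. Here two sections lead to two numbers unless the model adjusts for baseline. A comparison of raw 12-month scores makes no correction for a baseline difference between arms, and a comparison of changes subtracts that difference in full. The two results are therefore separated by whatever baseline difference the randomisation of 40 teams produced. If the choice is left open, it could be made once both results are known.

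There is also some avoidable loss of precision. Unless the correlation between baseline and 12 months is 0 or 1, neither form uses the baseline score as well as a model that estimates its coefficient.

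**Working it through.** **The plan's own figure.** 40 clusters × 27 patients = 1080 is arithmetically consistent. It cannot be reproduced from its inputs, because no planning SD is stated. Taking the baseline SD of 0.97 (Table 6) as an assumption, with a difference of 0.4, two-sided alpha 0.05 and 80% power, the need is 93 per arm. With design effect 1 + 26 × 0.05 = 2.3 this gives 93 × 2 × 2.3 = 428 patients, or 476 allowing for 10% loss. For the MRC >2 third alone (9 per cluster, design effect 1.4) the need is 290 in the subgroup, so 870 overall. Nothing here contradicts 1080.

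**Size of the gap between the two definitions.** Inputs: SD 0.97 (Table 6), ICC 0.05 (Sample size calculation), 1086 patients in 40 clusters (Baseline results), and arms treated as equal (actual 554 and 532).

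- Mean cluster size: 1086/40 = 27.15. Design effect: 1 + 26.15 × 0.05 = 2.31.
- SE of the between-arm baseline difference: 0.97 × √(4 × 2.31/1086) = 0.089.
- 95% range: ±1.96 × 0.089 = about ±0.18, or 44% of 0.4. Expected absolute size: 0.089 × 0.80 = 0.07.
- Sensitivity: with ICC 0 the SE is 0.97 × √(4/1086) = 0.059. With SD 1.1 (the postal CCQ) it is 1.1 × √(4 × 2.31/1086) = 0.101. Cluster sizes from 11 to 79 would raise it (about 0.096 for an assumed coefficient of variation of 0.5). Pair matching, ignored here, may lower it.
- In the MRC >2 third, assuming the same SD: N = 1086 × 0.334 = 363, design effect 1.40, SE 0.121, 95% range about ±0.24.

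If both definitions are analysed unadjusted in the same patients, their estimates differ by exactly this baseline difference, whatever the correlation.

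**How each estimate moves, given an imbalance b.** With correlation r and equal variances, the 12-month contrast shifts by r × b and the change contrast by −(1 − r) × b. For b = 0.175 (1.96 SE) and assumed r of 0.5 to 0.8, the shifts are +0.09 to +0.14 and −0.09 to −0.035. For the typical b = 0.07 and r = 0.6, they are about +0.04 and −0.03.

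**Precision.** Patient-level variance factors relative to the unadjusted 12-month score are 1 (12-month score), 2(1 − r) (change) and 1 − r² (baseline-adjusted). Adjusted over change is (1 − r²)/(2(1 − r)) = (1 + r)/2.

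| r (assumed) | 12-month | change | adjusted | adjusted ÷ change |
|---|---|---|---|---|
| 0.5 | 1 | 1.0 | 0.75 | 0.75 |
| 0.6 | 1 | 0.8 | 0.64 | 0.80 |
| 0.7 | 1 | 0.6 | 0.51 | 0.85 |
| 0.8 | 1 | 0.4 | 0.36 | 0.90 |

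A simulation checked that clustering does not overturn this (40 equal clusters of 24, ICC 0.05, SD 0.97, least squares with the individual baseline as covariate). Standard errors for 12-month, change and adjusted were 0.090, 0.092 and 0.079 at r = 0.5, and 0.092, 0.071 and 0.066 at r = 0.7. With r = 0.7 but a cluster-level correlation of only 0.2 they were 0.094, 0.099 and 0.088. The adjusted estimate had the smallest SE in every scenario tried.

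**Why adjustment removes the conflict.** Write Y for 12-month CCQ, X for baseline CCQ and T for arm. The model Y − X = a + τT + βX rearranges to Y = a + τT + (β + 1)X. The treatment effect τ is the same for either response.

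**The case against.** The best defence is that the sections describe different things: one names the instrument and time point, the other the contrast. The Time points section fixes 12 months in either case, and both wordings are compatible with a baseline-adjusted model. This stands in part. It means the plan is not committed to a poor analysis. But each sentence says what the primary outcome is, and the analysis section does not say which one governs.

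Several stronger readings are tempting, and the document does not support them.

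- **The change score will be analysed unadjusted.** The article does not say so. It lists no covariates, and a condensed article commonly leaves these to the analysis plan.
- **The change score or the 12-month score is biased.** Under randomisation both are unbiased. The shifts above are conditional on a given imbalance.
- **A large imbalance is likely.** A difference of 0.18 or more is a two-SE event, expected in about 5% of randomisations. The ICC of 0.05 is also the top of the range that the authors cite.
- **Recruitment after allocation created imbalance.** The Informed consent section says "The informed consent was acquired before the course took place and the practices started with their intervention". It does not say whether consent came before or after randomisation.
- **Every patient has a baseline CCQ.** Table 6 gives no completeness count for it.
- **The primary comparison is short of power.** For the unadjusted 12-month score with 10% loss, whole-sample power is 0.99 at SD 0.97 and 0.97 at SD 1.1.

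**Conclusion.** The conflict is in the text and should be resolved. It is a free improvement, not a flaw that threatens the trial. Without adjustment, the two definitions would typically differ by about 0.07 CCQ points and rarely by more than 0.18, against 0.4. That rests on SD 0.97, ICC 0.05, near-equal clusters and no credit for matching.

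The precision gain is certain in direction but not in size, because the article gives no baseline-to-12-month correlation. For an assumed 0.5 to 0.8, the patient-level variance is 10% to 25% below that of the change score, and the advantage over change vanishes as the correlation approaches 1. Adjustment deals only with imbalance in measured baseline CCQ. Other differences between teams, or selective recruitment, would remain. The conflict gives no ground for calling 1080 wrong.

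**What to change.** State one primary estimate, in the same words, in the Primary outcome and Sample size calculation sections: the between-arm difference in CCQ total score at 12 months, from a multilevel model with study-baseline CCQ as covariate. Say in the sample size section that the 0.4 refers to this difference.

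Identify the covariate as the study-baseline score (Table 6, mean 1.50, SD 0.97). The postal score returned with the invitation (Table 5) should not serve, since it was available for only 961 of the 1086 patients. Add one sentence on how a missing baseline is handled. A team-mean baseline term may be added, if decided in advance.

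Settle the wording before any 12-month comparison by arm is seen. The cost is a few sentences. CCQ is already scheduled at both visits, so no further patients or measurements are needed.

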### Randomization

Cluster randomization was at the level of the primary care team. The first author recruited the practices, and the selected participants were checked by the GP against formal inclusion and exclusion criteria before the intervention started. To enhance comparability between the intervention and control group, the clusters were matched and randomized by a researcher who was blinded to the identity of the practices. Matching was into pairs according to the following criteria: (i) percentage of patients from ethnic minorities, (ii) type of practice, (iii) practice location (urban/rural), (iv) age of GP, and (v) gender of the GP. Subsequently, the matched practices were randomized to the intervention group or the control group by using a computer-generated random number list.

### Informed consent

Informed consent was provided by the GPs and the patients. The informed consent was acquired before the course took place and the practices started with their intervention.

### Blinding

Because of the nature of the intervention, it is not possible to blind patients and primary care providers to practice group allocation. Therefore, blinded research nurses assess the outcomes. Patients are instructed not to report on their type of management to the outcome assessors.

## Data analysis at baseline

### Non-participation analysis at baseline

We recruited potential participants with an invitation letter including a postal CCQ questionnaire. Returned questionnaires were analysed to investigate if there were differences between participants and patients who fulfilled inclusion criteria, but refused to participate in the trial (non-participants). We compared differences on CCQ scores, sex and age using independent t-tests and chi-square tests.

## Analysis plan

### Analysis of effectiveness at 12 and 24 months

The final analysis of the trial will be carried out on an intention-to-treat basis. The freedom of the clusters to fill in the precise implementation of the intervention will probably relate to the (cost)-effectiveness of the intervention and, therefore, the clustering of patients in GP practices should be taken into consideration in the analysis [42]. Therefore, the results will be investigated with respect to the differences in intensity between and within clusters over time using multi-level analysis.

### Pre-planned subgroup analyses

We will study the influence of age, sex, disease burden (MRC score 1–2 vs. 3–5), disease severity (GOLD stage), and socioeconomic status. The trial was specifically powered on the MRC 1–2 vs. 3–5 subgroup analyses; see ‘Sample size calculation’.

### Economic evaluation at 12 and 24 months

The economic evaluation will be performed according to the internationally agreed guidelines [43] and the national guidelines for pharmacy-economic research [44]. We will calculate the costs from a healthcare perspective and a broad societal perspective, in order to facilitate decision making. The healthcare perspective will include all costs covered by the healthcare sectors budget: development, implementation and healthcare utilization costs. The costs from societal perspective will include travel and productivity costs in addition to the costs from the healthcare perspective to capture (almost) all costs related to the intervention, irrespective of who actually bears them.

The healthcare utilization costs (excluding medication costs), travel costs and productivity costs of patients will be calculated using questionnaires at different time points (Table 2). These questionnaires will collect self-reported cost-related data by patients using a recall period of three months. Additionally, the type and amount of medication from the individual patients will be collected from the GP information systems. The unit costs per medication prescription will be based on the GIP Databank [44]. Time and material resources associated with the training of the healthcare providers, the multidisciplinary team meetings in the GP practices, and the ICT support will be estimated based on course attendance, computer-documented minutes of ICT use, treatment plans, and professional self-report. Finally, the productivity costs will be estimated using the friction method, which implies that the costs of absenteeism will occur only for a fixed (friction) period ending at the moment that the employee is replaced [45].

### Cost-effectiveness (CEA) and cost-utility analyses (CUA)

The relation between the costs and the estimated health outcomes is expressed in cost-effectiveness ratios: (1) costs per QALY, (2) costs per exacerbation prevented, (3) costs per patient with a clinically relevant improvement of at least 0.4 units on the CCQ, (4) costs per patient with a clinically relevant (4 units) improvement on the SGRQ, and (5) costs per patient with a 1 point improvement on the MRC dyspnea scale. Adopting such a wide range of outcome measures in the economic evaluation is in line with recent guidelines of a joint ATS/ERS task force on outcome measurements in COPD that recommend taking a multi-outcome approach [46]. At the same time, comparison with the cost-effectiveness of other interventions for other diseases is made possible through the calculation of costs per QALY. Uncertainty around cost-effectiveness ratios will be dealt with in probabilistic sensitivity analysis in which costs and health outcomes will be bootstrapped and plotted on cost-effectiveness planes from which cost-effectiveness acceptability curves will be drawn [47-49]. In additional ‘net monetary benefits’ [50] will be calculated using different thresholds of the willingness to pay for a QALY and it will be investigated which patient, practice and team characteristics are related to the size of the net monetary benefits. The economic evaluation will compare differences in costs to differences in effects (CEA) and quality adjusted life-years (CUA). The analysis will have a 12 and 24-months time horizon. Sensitivity analyses will be performed on the perspective (societal versus healthcare) and the applied utility measure (Dutch EQ5D).

## Baseline results

### Primary care practices

The characteristics of the enrolled 54 general practices, which formed 40 clusters, are shown in Table 3. Numbers of included patients per participating cluster ranged from 11 to 79 patients. Most practices were single-handed (44%) or one or more partner practices (41%). The enrolled practices included a total of 76 participating GPs; the majority (61%) were males with a mean age of 50 (range 35–62) years and 16 (SD 8.2) years of practicing.

**Table 3 T3:** Characteristics of included primary care practices in the RECODE study

**General practices**	
Number of GP practices	54
Number of clusters	40
Number of included patients per participating cluster, range	11-79
Type of practice,%	
Single-handed practice	44
One or more partner practice	41
Healthcare centre	15
Practice location,% urban	72
Patient practice population, n (range)	3418 (1750-16907)
Ethnic minorities,%	15
**General practitioners**	
Number of participating GP’s	76
Gender GP,% male	61
Age GP, years (range)	50 (35-62)
Years practicing, years (SD)	16 (8.2)

## Current level of care of the practices

We assessed the current level of COPD care at baseline in all general practices to be able to report any difference in quality of care after 12 months. Results at baseline are shown in Table 4. Almost half of the RECODE patients (53%) have a registered smoking status; however, a standard spirometry test in the last year was less common, with only (12%) of the patients receiving spirometry.

**Table 4 T4:** Description of current level of care of included GP practices: distribution of the performance indicators of the practices

**Measurement category**	**Process indicator**	**% (SD)**
Smoking	% RECODE patients with registered smoking status	53 (27.9)
	% RECODE patients that are registered smokers	35 (19.3)
	%RECODE patients, which are registered smokers with stop-smoking advice in the last year	35 (34.3)
BMI	% RECODE patients of which the BMI is measured in the last year	42 (23.8)
Treatment & monitoring	% RECODE patients with inhalation technique controlled in the last year	13 (20.3)
	% RECODE patients with a spirometry test in the last year	12 (14.9)
	% RECODE patients with monitored functioning with a structured method ( CCQ or MRC) in the last year	28 (27.4)
	% RECODE patients with controlled physical activity in the last year	30 (24.9)

